## Abstract

**Background:**

Acute pancreatitis (AP) is an inflammatory disorder that causes a considerable economic health burden. While the overall mortality is low, around 20% of patients have a complicated course of disease resulting in increased morbidity and mortality. There is an emerging body of evidence that the microbiome exerts a crucial impact on the pathophysiology and course of AP. For several decades multiple clinical and laboratory parameters have been evaluated, and complex scoring systems were developed to predict the clinical course of AP upon admission. However, the majority of scoring systems are determined after several days and achieve a sensitivity around 70% for early prediction of severe AP. Thus, continued efforts are required to investigate reliable biomarkers for the early prediction of severity in order to guide early clinical management of AP patients.

**Methods:**

We designed a multi-center, prospective clinical-translational study to test whether the orointestinal microbiome may serve as novel early predictor of the course, severity and outcome of patients with AP. We will recruit 400 AP patients and obtain buccal and rectal swabs within 72 h of admission to the hospital. Following DNA extraction, microbiome analysis will be performed using 3rd generation sequencing Oxford Nanopore Technologies (ONT) for 16S rRNA and metagenomic sequencing. Alpha- and beta-diversity will be determined and correlated to the revised Atlanta classification and additional clinical outcome parameters such as the length of hospital stay, number and type of complications, number of interventions and 30-day mortality.

**Discussion:**

If AP patients show a distinct orointestinal microbiome dependent on the severity and course of the disease, microbiome sequencing could rapidly be implemented in the early clinical management of AP patients in the future.

*Trial registration*: ClinicalTrials.gov Identifier: NCT04777812

## Background

Acute pancreatitis (AP) is an inflammatory disorder that causes a considerable economic health burden [1]. While the majority of AP show a mild clinical course, about 20% of patients suffer from moderate or severe disease with major local and systemic complications and a prolonged hospital stay [2, 3]. Furthermore, severe pancreatitis is associated with a dramatic increase of mortality ranging between 36 and 50% [4–6]. The revised Atlanta classification is a feasible scoring system to distinguish between mild, moderately severe and severe pancreatitis [3]. However, the revised Atlanta classification is determined in retrospect and does not guide early clinical management and risk assessment. For several decades multiple clinical and laboratory parameters have been evaluated, and complex scoring systems were developed to predict the clinical course of AP upon admission. However, scoring systems such as the *Ranson score*, *Acute Physiology and Chronic Health Evaluation II score* (APACHE II), *Bedside Index for severity in acute pancreatitis* (BISAP), *Harmless acute pancreatitis score* (HAPS), *Pancreatitis Activity Scoring System* (PASS) and the *Baltharzar-Score* mostly achieved a sensitivity around 70% for early prediction of severe AP [7–12]. Thus, continued efforts are required to investigate reliable biomarkers for the prediction of severity in order to guide early clinical management of AP patients.

There is an emerging body of evidence that the microbiome exerts a crucial impact on the pathophysiology of different pancreatic diseases [13]. Normal pancreas tissue and pancreatic ductal adenocarcinoma (PDAC) harbor distinct compositions of microbiota [14, 15]. Regarding PDAC, the orointestinal and tumoral bacteria and fungi interact with the tumoral immune system, thus influencing progression and overall survival [15–17]. Furthermore, Geller et al. postulated among others that response to chemotherapy depends on the presence of certain bacteria [18]. Using a mouse model Pushalkar et al. demonstrated that bacteria from the oral cavity can migrate into the PDAC [15]. Moreover, a number of cross sectional trials support the hypothesis that oral microbes can be used as a non-invasive diagnostic tool to distinguish PDAC from CP or other premalignant pancreatic lesions such as intraductal papillary mucinous neoplasm (IPMN) [13]. Taken together, there are several recently described associations between PDAC and the microbiome from the oral cavity and the gut.

Only a few studies have focused on the influence of the orointestinal microbiome on inflammatory pancreatic diseases. Due to a systemic inflammatory response syndrome (SIRS) and hypovolemia more than 60% of AP patients suffer from a condition called “leaky gut” [19]. Consequently, circulating microbes can aggravate SIRS. In line with the expected microbiome alterations, two small studies have analyzed feces from AP patients postulating a significantly different intestinal microbiome between healthy volunteers and AP patients, and between mild and severe AP [20, 21].

We aim to comprehensively investigate the orointestinal microbiome as a predictor of course, severity and outcome of patients with AP. In a prospective, multicentric interventional trial we aim to recruit a sufficient number of patients and analyze both the oral and intestinal microbiome by metagenomic and 16S rRNA sequencing.

## Methods: participants, interventions, and outcome

### Study setting

This study is a multicentric prospective study initiated and coordinated from the University Medical Centre Goettingen and supported by the AG Pancreas of the German Society for Digestive and Metabolic Diseases (DGVS) and the European Pancreatic Club (EPC). To date, seven German University Hospitals (LMU Munich, Technical University Munich, Leipzig, Greifswald, Halle, Rostock, Goettingen) and one District Hospital (Hann. Münden) are actively recruiting patients. The principal investigator intends to include more centers across Germany and Europe. All collected samples will be sent to Goettingen where wet-bench and bioinformatical analyses will be conducted. The study was registered 2nd March 2021 (retrospectively) at the US National Library of Medicine at https://www.clinicaltrials.gov (NCT04777812).

### Eligibility criteria

Patients with AP (2 out of 3 following diagnostic criteria: lipase > 3 × of upper limit (> 280U/l), abdominal pain, and imaging modalities (computed tomography (CT), magnetic resonance imaging (MRI) or ultrasound)) indicating AP will be included within 72 h after hospital admission. In our study, amylase elevation will not considered as a diagnostic criterion. In most cases, the first two criteria lead to the diagnosis of AP. Only in rare cases one of the above-mentioned imaging tools will aid to diagnose AP. Typical ultrasound features are: increased volume (> 2.4 cm in pancreas-body diameter), decreased echogenicity and peripancreatic fluid collection [22]. CT and the MRI indicate AP if parenchymal enlargement (diffuse or localized), alterations in density, diffuse margins, acute peripancreatic fluid collection and/or surrounding fat stranding are reported [23]. All recruited patients will sign the informed consent form before buccal and rectal swab collection. Pregnant women, patients < 18 years and patients who are incapable of giving consent will be excluded. The last-mentioned group includes patients who are not authorized to give consent due to psychological or other diseases. Patients who show signs of chronic pancreatitis (CP) on imaging will also be excluded.

The intake of antibiotic and probiotic medication will be recorded before the collection of the swabs and will not be considered as exclusion criteria. Patients will be categorized in 5 groups according to the time of antibiotic medication: current, within the last week, more than 1 week and less than 6 month ago, and more than 6 months ago. Together with other drugs and reported diseases the anti- and probiotic intake will be statistically associated with the orointestinal microbiome patterns and thus treated as potential confounder. Table 1 summarizes medical history and previous medication that is recorded for each patient.

**Table 1 Tab1:** Medical history and previous medication

Medical history	Previous medication
Cardiovascular diseases (e.g. coronary artery disease, peripheral artery disease, TIA, apoplex)	Metformin
Heart failure	Insulin
Diabetes mellitus	Other antidiabetics
Inflammatory bowel disease	PROTON-pump inhibitors (including occational intake)
Irritable stomach and/or bowel disease	Immune suppressors (including topical immune suppressors affecting intestinal tract)
Clostrioides difficile infection within last year	Antidepressants
Chronic constipation	Neuroleptics
Chronic diarrhea	paracetamol (including occational intake)
Liver cirrhosis	NSAIDs (including occational intake)
Cholestasis	Opiates (including occational intake)
Gastrointestinal malignancy (pancreas, liver and bile duct inclusive)	LAXATIVE (INCLUDING OCCATIONAL INTAKE)
Extraintestinal solid malignancy	Statins
Hematological malignancy	Probiotics
Bariatric surgery	Antibiotics
Other abdominal surgery	
HIV	
Rheumatic disease (arthritis, connective tissue disease, vasculitis)	
Current alcohol use disorder	
Former alcohol use disorder	
Nicotine abusus	

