### Outcomes

This prospective translational study aims to evaluate the orointestinal microbiome as a potential biomarker for the course, severity and outcome of patients with AP. From each patient one buccal and rectal swab will be collected within 72 h after hospital admission. As primary endpoint we will analyze the association between microbial composition and the revised Atlanta classification. Secondary endpoints will be the association between microbiome signatures and length of hospital stay, numbers of interventions and mortality. For these analyses, alpha and beta diversity of microbiota will be determined and compared between mild, moderately severe and severe AP. If the analysis will reveal a set of microbes whose presence or abundancies are able to distinguish among the revised Atlanta classification (differential abundances), the microbiome could be employed as early clinical biomarker to guide clinical management of AP patients (e.g. early use of antibiotics).

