### Statistical methods

Prior statistical testing, normal distribution and homogeneity of variance will be examined using, QQ-plots and Levene’s test, respectively. If the data will be considered as normally distributed and the homogeneity is not violated, t-test for two groups and ANOVA with consecutive post-hoc tukey-type multiple comparisons for data with more than two groups will be performed. Non-normally distributed variables will be compared with Wilcoxon rank test (two groups) or non-parametric multiple comparisons (Kruskal–Wallis) for more than two groups. Statistical methods will compare groups for primary and secondary outcomes. For alpha diversity the following parameters will be calculated and presented in boxplots: Shannon-Index, Chao1-Estimator and observed richness (i.e. species). For beta diversity the following distances metrics will be performed: Bray–Curtis, unweighted and weighted UniFrac distances. The beta diversity will be visualized with principal coordinate analysis plot (PCoA). Significances will be calculated using PERMANOVA and pairwise adonis test. Further investigation of a significant distance in beta diversity will be conducted with high dimensional class comparisons using linear discriminant analysis of effect size (https://huttenhower.sph.harvard.edu/lefse/). Furthermore, a microbial network will be constructed after centered log-ratio transform of the out-table and visualized with Cytoscape.

Measures of diagnostic and predictive accuracy will be calculated, including area under the curve (AUC) and optimal cut-off point for classification (using simultaneous maximization of sensitivity and specificity).

Cox regression will be performed to interrelate length of hospital stay and the microbiome patterns, which will be calculated and will be most distinctive for the study population. 30-days mortality will also be analyzed using Cox-Regression with a calculated set of microbes as regressors. Number of interventions will be analyzed using negative binomial regression with the same microbes as regressors. Whenever feasible, 95-% confidence intervals will be provided for estimates.

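### Drugs are declared potential confounders of the microbiome–severity association, but the severity comparisons listed name no drug term, so a drug effect can pass for a severity signature

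*Protocol article*

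**What the plan says.** All references are to the protocol article.

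- **Eligibility criteria.** Antibiotic and probiotic intake "will be recorded before the collection of the swabs and will not be considered as exclusion criteria". The text groups the rest of the medication and medical history with these and states that "the anti- and probiotic intake will be statistically associated with the orointestinal microbiome patterns and thus treated as potential confounder". The recorded items, set out in Table 1, include proton-pump inhibitors, opiates and antibiotics. Antibiotic use is to be put into five groups by timing, but the list has four: "current, within the last week, more than 1 week and less than 6 month ago, and more than 6 months ago".
- **Outcomes.** "As primary endpoint we will analyze the association between microbial composition and the revised Atlanta classification". On timing: "From each patient one buccal and rectal swab will be collected within 72 h after hospital admission".
- **Statistical methods.** Where normality and equal variances hold, "t-test for two groups and ANOVA with consecutive post-hoc tukey-type multiple comparisons for data with more than two groups will be performed"; otherwise Wilcoxon or Kruskal–Wallis. The section applies these group comparisons to primary and secondary outcomes. Beta diversity is tested by PERMANOVA and pairwise adonis, and a significant distance is followed by "high dimensional class comparisons using linear discriminant analysis of effect size" (LEfSe). An AUC and an optimal cut-off follow. Cox and negative binomial regression are for secondary outcomes, and microbiome patterns or microbes are the only regressors named.

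**The concern.** A drug confounds the microbiome–severity association when it is related both to the microbiome and to severity. The Eligibility criteria describe a check of the first link only, and the word *thus* presents that check as the handling. Nothing in it looks at the link between drug and severity or removes the drug's contribution from the comparison of Atlanta classes. The section that lists the tests does not close the gap.

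The sampling window sharpens this. A swab at up to 72 h can follow treatment begun in hospital. The *current* antibiotic category can therefore combine patients already on antibiotics at admission, for whom antibiotics are a possible confounder, with patients started on them after admission because they were ill, for whom they may be a consequence of severity. The two call for different analyses.

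At stake is the primary endpoint. The Outcomes section hopes that a discriminating set of microbes could guide management and gives early antibiotic use as an example. A signature produced partly by antibiotics already given would be circular for that purpose.

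**Working it through.** **1. The plan's own figure.** The only calculation is the power for an AUC of 0.8 against 0.7 with 100 per group, one-sided 2.5%, stated as 85%. With the Hanley–McNeil standard error on the logit scale:

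- SE(0.8) = 0.0314, divided by 0.8 × 0.2 = 0.196
- SE(0.7) = 0.0368, divided by 0.7 × 0.3 = 0.175
- logit(0.8) − logit(0.7) = 1.386 − 0.847 = 0.539
- power = Φ[(0.539 − 1.96 × 0.175) / 0.196] = Φ(0.995) = 84%

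This agrees with the stated figure. It does not bear on confounding: power describes precision for an AUC, not what that AUC reflects.

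**2. Can each listed severity analysis carry a drug term?**

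| Analysis named | Drug term named? | Could it take one? |
|---|---|---|
| t-test, Wilcoxon, Kruskal–Wallis | No | No |
| ANOVA with Tukey comparisons | No | Yes, if extended with factors or covariates |
| PERMANOVA, pairwise adonis | No | PERMANOVA yes |
| LEfSe | No | Only by stratifying through a subclass |
| AUC and cut-off | No | Only through a model feeding it |

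**3. What an omitted drug term can do.** Inputs from the Sample size section: 300 mild and 100 moderately severe or severe patients. Assumptions: no true severity effect; an alpha-diversity index with SD 1 given drug use; antibiotics lower it by δ SD; use is p0 in mild and p1 in more severe patients; two-sided 5% test.

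A normal approximation shows the mechanism:

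- spurious mean difference D = δ(p1 − p0)
- group variance = 1 + δ²p(1 − p)
- SE = √(var1/100 + var0/300)
- rejection rate = Φ(D/SE − 1.96) + Φ(−D/SE − 1.96)

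*Small imbalance* (20% against 30%, δ = 0.5): D = 0.5 × 0.10 = 0.05; SE = √(1.0525/100 + 1.04/300) = 0.118; D/SE = 0.42; rejection 7%.

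*Large imbalance* (10% against 50%, δ = 0.8): D = 0.8 × 0.40 = 0.32; SE = √(1.16/100 + 1.0576/300) = 0.123; D/SE = 2.60; rejection 74%.

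Simulation of the Wilcoxon test (1,500 to 3,000 runs per setting) agrees within simulation error:

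| Use, mild vs more severe | Shift (SD) | Unadjusted rejection |
|---|---|---|
| 20% vs 20% | 0.3–1.0 | 5–6% |
| 20% vs 30% | 0.3 | 5% |
| 20% vs 30% | 0.5 | 6% |
| 10% vs 30% | 0.5 | 12–13% |
| 20% vs 50% | 0.5 | 23% |
| 10% vs 50% | 0.5 | 37–39% |
| 10% vs 50% | 0.8 | 73% |

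A linear model adjusted for antibiotic use rejects in 4–6% of runs throughout. A further setting at 20% against 60% and 1.0 SD gives 88% unadjusted, with a mean AUC of about 0.61 where the true severity effect is nil.

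**4. The antibiotic variable.** The announced count is five and the listed categories are four. None is for patients without antibiotic exposure, and none gives the start of treatment relative to admission.

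**The case against.** **The article states an intent to handle confounding.** It records 14 drug classes and 20 history items and calls them potential confounders. A reader might infer that association testing is the whole plan; the text does not support that. Nor does it say that the PERMANOVA will be run unadjusted. Covariate lists and permutation schemes are commonly left to an analysis plan, and none is shown here. This stands for PERMANOVA and ANOVA, where silence on covariates alone would be no finding. It does not stand for the section as a whole, which fixes group tests for the primary outcome that cannot adjust, after the Eligibility criteria have inferred confounder handling from a drug–microbiome association. Those two statements do not fit together.

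**Bias is not certain.** A reader might infer that drug effects will appear as a severity signature. The document gives neither drug-use rates by Atlanta class nor effect sizes. With balanced use there is no inflation, and with a small imbalance almost none. The high rates come from large assumed imbalances. This stands in full.

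**A predictor need not be causal.** This is true, but the stated aim is an early microbiome biomarker. An AUC that partly reflects treatment already given does not show what the microbiome adds.

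**The four-for-five count may be a reporting slip**, most plausibly a missing group for no exposure, and start dates may be captured on a form that is not shown. Both are possible. The count still needs correcting, because this variable would carry the adjustment.

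**Conclusion.** The concern holds as a mismatch within the document. Drugs and diseases are declared potential confounders, the handling described addresses only their link to the microbiome, and no severity comparison listed names a drug term; three of the tests cannot take one. A drug effect can therefore appear as a severity signature if drug use at swab time differs by Atlanta class and the drug shifts the microbiome.

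The size is unknown. On the assumptions above, with a single drug and one alpha-diversity index, the range is from practically nominal to a large majority of null trials declared positive. What does not depend on those assumptions is that adjustment holds the error near its nominal level when the drug is measured and modelled correctly. Because the primary endpoint is affected and most of the data needed are already recorded, the change should be made before analysis.

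**What to change.** 1. **Primary PERMANOVA:** include a short pre-specified set of covariates already recorded, namely antibiotic category and proton-pump inhibitor use, with centre as a term or as a permutation stratum. Report the severity term after these.
2. **Alpha diversity:** use regression with the same covariates in place of, or beside, the unadjusted group tests.
3. **Differential abundance:** add a covariate-adjusted analysis beside LEfSe. LEfSe need not be dropped.
4. **Antibiotic variable:** reconcile the announced five groups with the four listed and say where unexposed patients belong. Where start dates are available, separate antibiotics started before admission from those started after.
5. **Sensitivity analysis:** repeat the primary analysis in patients without current antibiotics.
6. **Eligibility criteria wording:** replace the inference from association to confounder handling with a reference to these adjusted analyses.

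**Cost.** Mostly wording, plus a few degrees of freedom. With about 100 non-mild patients and at least eight centres, the covariate set must stay short; entering all of Table 1 would not be workable. The start-time split may be missing for patients already enrolled, since centres are recruiting and uploaded data cannot be altered. Adjusting for antibiotics started after admission may also remove part of a real severity signal, so adjusted and unadjusted results should be shown together. The analysis without current antibiotics is smaller and less precise.

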### Outcomes

This prospective translational study aims to evaluate the orointestinal microbiome as a potential biomarker for the course, severity and outcome of patients with AP. From each patient one buccal and rectal swab will be collected within 72 h after hospital admission. As primary endpoint we will analyze the association between microbial composition and the revised Atlanta classification. Secondary endpoints will be the association between microbiome signatures and length of hospital stay, numbers of interventions and mortality. For these analyses, alpha and beta diversity of microbiota will be determined and compared between mild, moderately severe and severe AP. If the analysis will reveal a set of microbes whose presence or abundancies are able to distinguish among the revised Atlanta classification (differential abundances), the microbiome could be employed as early clinical biomarker to guide clinical management of AP patients (e.g. early use of antibiotics).

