### Participant timeline

Within 72 h after hospital admission, one buccal and rectal swab will be collected for analysis of the microbiome. Patients will be followed up until their discharge and categorization into mild, moderately severe and severe AP will be performed at the day of discharge.

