### Recruitment

AP patients will be usually treated on gastroenterology or surgical wards. Thus, all participating centers will have access to AP patients on their wards. Furthermore, there is a cooperation between the local principal investigators (PIs) and the emergency room, and PIs will be given immediate notice if patients will have to be directly submitted to IMC or ICU. Therefore, local PIs will be aware of most AP patients admitted to their centers and will be able to enroll them for this study after written informed consent.

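### Swabs may be taken up to 72 h after admission with no requirement that moderately severe or severe disease be absent, so the pooled AUC can mix recognition of manifest disease with early prediction

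*Protocol article*

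**What the plan says.** **Purpose.** The abstract (Methods) sets out to "test whether the orointestinal microbiome may serve as novel early predictor of the course, severity and outcome of patients with AP". The abstract's Background criticises existing tools because "the majority of scoring systems are determined after several days". The Sample size section bases the 400 patients on an AUC that it describes as measuring how well outcomes are predicted.

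**Timing of the index sample.** Under Outcomes, "one buccal and rectal swab will be collected within 72 h after hospital admission". Under Eligibility criteria, patients with findings "indicating AP will be included within 72 h after hospital admission". The clock starts at admission.

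**Timing of the outcome.** Under Participant timeline: "Patients will be followed up until their discharge and categorization into mild, moderately severe and severe AP will be performed at the day of discharge". The Background section says what marks the worse classes: "about 20% of patients suffer from moderate or severe disease with major local and systemic complications and a prolonged hospital stay".

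**Who may enter.** The exclusions are pregnancy, age under 18, inability to consent, and signs of chronic pancreatitis on imaging. None concerns a complication already present. A peripancreatic fluid collection is listed among the imaging signs that support the diagnosis. Under Recruitment, "PIs will be given immediate notice if patients will have to be directly submitted to IMC or ICU".

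**Analysis.** Statistical methods names the AUC and an optimal cut-off. It mentions no separation by time of swab or by severity at swab.

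**The concern.** A predictor has to be measured before the event it predicts. Here the sample can come up to three days into the stay, and the outcome is graded at discharge from a course that includes those three days. A patient whose complication appeared on day 1 and who was swabbed on day 3 counts as a correctly predicted case if the microbiome differs, although the complication was already there when the sample was taken.

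The stake is the conclusion, not the conduct of the study. The Outcomes section moves from a difference between Atlanta classes to use as an early biomarker for guiding management. If part of the AUC comes from patients already in the worse class at swab, the pooled figure does not say how well the swab identifies patients who will later deteriorate, which is the use the article has in view.

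**Working it through.** **1. The plan's own figure.** Inputs from Sample size: true AUC 0.8, 100 per group, one-sided 2.5%, stated power 85% against 0.7 and 99% against 0.6, 95% interval 0.735 to 0.855.

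Check by simulation (equal-variance binormal scores, DeLong standard error, 6,000 runs, 100 per group):
- mean standard error 0.0308;
- power against 0.7 of 83.2% on the logit scale and 87.1% with a Wald interval;
- power against 0.6 above 99.9%;
- mean logit limits 0.733 and 0.854.

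The stated figures reproduce closely. The sample-size arithmetic is not the problem; the question is which quantity the AUC estimates.

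**2. What the pooled AUC estimates.** The AUC is the probability that a random case scores above a random control. Let q be the share of Atlanta II–III cases already manifest at swab. With one score and the same controls:

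AUC(pooled) = q × AUC(manifest) + (1 − q) × AUC(not yet manifest)

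so AUC(not yet manifest) = [AUC(pooled) − q × AUC(manifest)] / (1 − q).

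Set AUC(pooled) to the planning value 0.80. Neither q nor AUC(manifest) is in the article; both are assumed. With AUC(manifest) = 0.90:
- q = 0.1: (0.80 − 0.09) / 0.9 = 0.789
- q = 0.2: (0.80 − 0.18) / 0.8 = 0.775
- q = 0.3: (0.80 − 0.27) / 0.7 = 0.757
- q = 0.5: (0.80 − 0.45) / 0.5 = 0.700

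Range over the assumed AUC in manifest cases:

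| q | 0.85 | 0.90 | 0.95 |
|---|---|---|---|
| 0.1 | 0.794 | 0.789 | 0.783 |
| 0.2 | 0.787 | 0.775 | 0.763 |
| 0.3 | 0.779 | 0.757 | 0.736 |
| 0.5 | 0.750 | 0.700 | 0.650 |

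If manifest cases were no easier to recognise (0.80), the predictive AUC would be 0.80 at every q. The distortion needs both a non-zero share and easier recognition.

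**3. Precision left for a restricted AUC.** A patient classed as mild at discharge, on the whole stay, has not met the worse criteria at swab, so the 300 planned controls remain and only cases are lost. Hanley–McNeil, with m cases and n controls:

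SE² = [A(1 − A) + (m − 1)(Q1 − A²) + (n − 1)(Q2 − A²)] / (mn), Q1 = A/(2 − A), Q2 = 2A²/(1 + A)

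Power = Φ{[0.8 − 0.7 − 1.96 × SE(0.7)] / SE(0.8)}

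For m = 100 and n = 300: SE(0.8) = 0.0283, SE(0.7) = 0.0321, and (0.1 − 0.0629) / 0.0283 = 1.31, which gives about 91%.

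| Cases | 300 controls | 100 controls |
|---|---|---|
| 100 | 91% | 81% |
| 80 | 84% | 74% |
| 50 | 65% | 57% |

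This formula runs below the simulation (81% against 83% to 87% for 100 per group), so the fall matters more than the level. These figures hold the true AUC at 0.8 in the remaining cases.

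**The case against.** **The primary endpoint is an association.** This stands. A difference in microbial composition between Atlanta classes is a valid finding whenever the swab was taken. The point reaches only the AUC and the conclusion about early use, and the article words that conclusion conditionally.

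**Treatment effects are already considered.** Eligibility criteria has antibiotic and probiotic intake recorded before the swab, with a category for current antibiotic use, and treats these together with other drugs and diseases as potential confounders. A reader might infer that in-hospital treatment is ignored; the article does not support that. But handling drug exposure does not separate manifest from future disease.

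**The number already manifest is unknown and may be small.** This stands. Excluding patients who cannot consent may remove some of the sickest. A reader might infer from the notice about direct IMC or ICU admissions that these patients already have organ failure when swabbed. The text says nothing of their status at swab, and early notice could equally mean an early swab. It is likewise not shown that swab delay differs by severity, or that most swabs are late: 72 h is a maximum. Nor is the critique of existing scores uniform, since the Background section also says that "complex scoring systems were developed to predict the clinical course of AP upon admission".

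**The magnitude is chosen.** A reader might go further and say that a weak predictor would reach the planning value: 0.6 × 0.90 + 0.4 × 0.65 = 0.80. The arithmetic is right, but all three inputs are assumed, and at 10% or 20% manifest the effect is modest.

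**The case report form and analysis plan may cover this.** They may, and the absence of form fields from an article is no fault. What the article does fix is the 72 h window, grading at discharge, and eligibility without an outcome-free condition.

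**Conclusion.** The point holds in limited form. Followed as written, the plan can credit disease already manifest at swab to an AUC presented as predictive, for a marker proposed as early. The positive group combines moderately severe and severe disease, so what may be recognised is either.

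Its size cannot be computed from the article. Under the assumed 0.90 for manifest cases, the gap from a pooled 0.80 runs from about 0.01 with 10% manifest to 0.10 with 50%. In the latter case the predictive AUC equals 0.70, the plan's own reference value. These figures also assume a single score applied to both kinds of case.

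A reader might infer that the AUC cannot support early prediction at all. The documents do not support that: if few cases are manifest at swab, the pooled and restricted figures will nearly agree. What is missing is a way to tell.

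**What to change.** Keep the 72 h recruitment window, all patients in the association analyses, and the pooled AUC. Then:

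1. Make sure two items are recorded at sampling: the time of swab, and whether organ failure or a known local complication was already present, with a not-assessed option. Under Data management, patient data are uploaded after discharge and cannot then be altered, so these items must be captured prospectively.
2. Beside the pooled AUC, report the AUC in patients who do not yet meet moderately severe or severe criteria at swab, and show results by time from admission to swab, for example within 24 h.
3. State that any conclusion about early prediction rests on the restricted AUC.

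**Cost.** Two form items and a few lines of analysis text. The restricted AUC has fewer Atlanta II–III cases, hence a wider interval and lower power than with the planned 100 cases, as tabulated above. Status at swab will also be partly misclassified: the article says imaging is needed for diagnosis only rarely, so a local complication may be unknown at that time. Both are reasons to report the restricted AUC next to the pooled one rather than in its place.
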